### Monitoring

A Data and Safety Monitoring Plan is in place for this study. Adverse events, enrollment numbers, lost to follow up counts, and withdrawals will be monitored by the Clinical Coordinator. A continuing review will also be completed annually. Any adverse events and deviations will be reported to the IRB and included in the continuing review. Any adverse effects or unanticipated problems will be reported to the study PI, the IRB, and the study sponsor in accordance with IRB policies. At all times, the IRB will be promptly provided with the information from the Clinical Coordinator as needed.

## Discussion

We anticipate that women engaged in the intervention will have a decreased oocyte expression of genes related to inflammation and oxidative stress and lower Indole-3-Proprionic Acid (IPA) content in follicular fluid compared to women who received the standard of care because of evidence demonstrating the positive effects of the Mediterranean diet on fertility rates and pregnancy outcomes [7, 20, 22]. We also expect that women engaged in the intervention will have greater fitness level, higher insulin sensitivity, lower triglycerides, lower blood pressure and lower systemic inflammation at the end of the intervention compared to women in the standard of care group. There is indisputable evidence on the beneficial effects of a Mediterranean diet and physical activity on chronic diseases like diabetes, cardiovascular disease, cancer, and neurodegenerative diseases [19, 37, 38]. Further, when both lifestyle factors are incorporated during the peri-conception period and followed throughout pregnancy greater protections may occur [38]. These findings suggest the importance of individualized interventions, with future RCT’s exploring interventions with both physical activity and Mediterranean-style eating patterns, especially in the pre-conception period to ensure best outcomes throughout pregnancy [38].

One study suggested better Mediterranean diet scores were positively associated with Luteal Phase Deficiency (LPD) after adjusting for age, percentage body fat, and total energy intake [39]. LPD may contribute to infertility and early miscarriage; one study suggested that diet quality may be associated with LPD among healthy eumenorrheic women, therefore further research is warranted to elucidate how dietary factors, such as Mediterranean style eating patterns, may influence LPD and other causes of infertility [39]. Emerging evidence suggests that a RCT with PA may improve pregnancy rates in women with reproductive health problems [11]. Comparative studies indicate that PA intervention may be as effective as other commonly used clinical intervention strategies for improving reproductive health outcomes. Preliminary findings suggest that PA may be an affordable and feasible alternative or complementary therapy to fertility treatments, while the type, intensity, frequency, and duration of optimal PA intervention, and the role of PA independent of weight loss, remain unclear [11].

Therefore, the need to further investigate how lifestyle factors including exercise, diet, and behavioral modifications affect fertility is imperative and more emphasis should be placed on physiological consequences of an unhealthy lifestyle during the critical peri-conception window. Future collaboration between research institutions, clinical practice, and communities will enable the implementation of more evidence-based recommendations and interventions such as counseling to improve dietary behaviors or nutritional programs aimed at reproductive aged populations and at risk groups like those undergoing fertility treatments [40]. Moreover, new evidence through larger more in-depth studies will support the development of lifestyle interventions to improve the health of mothers and their offspring from the earliest moment in life [41]. Thus, given the potential of the intervention being tested for adoption into clinical practice, it may help women suffering with overweight or obesity and infertility.

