**Methods:**

This single blinded randomized control trial will include 120 women with a BMI of 25–45 kg/m^2^, ≥21 years of age, and undergoing in vitro fertilization (IVF) treatments. Participants will be randomized to standard of care (*N* = 60) or an intervention group (*N* = 60) in a block design by polycystic ovary syndrome status. The intervention will combine a dietary component (Mediterranean meal plan) with exercise prescription following the Physical Activity Guidelines for Americans. Participants will be assessed pre- and post-intervention. The standard of care group will be offered to join the intervention group if the IVF treatments are unsuccessful as a cross over design. Recruitment is anticipated to start in July of 2021. Primary outcomes will include single oocyte gene expression profiles and follicular fluid metabolites. Mann-Whitney U nonparametric tests will be used to assess potential differences for each stratum. Follicular fluid and serum metabolites will be analyzed using a one-factor Analysis of Covariance (ANCOVA) at four levels, pair-wise comparisons using Tukey-Kramer post-hoc tests will be used to identify groups whose means differ significantly while retaining the family-wise error rate at 5%. When the design is balanced, two-way Analysis of Variance (ANOVA), or non-parametric Friedman test will be used in data analysis. Additionally, general linear models and ANCOVA may be used to control for covariates. Significance will be set at *p* < 0.05. Findings will be disseminated via peer-reviewed manuscripts and presentations at scientific conferences.

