Models of diet-induced obesity in mice have shown that exercise improves, but does not reverse, damage imparted on oocytes as a result of a high fat diet [10]. A systematic review and meta-analysis of human studies found that exercise improved pregnancy rates (risk ratio 2.10, 95% CI: 1.32–3.35) in women with reproductive health problems like polycystic ovary syndrome (PCOS) [11]. Studies have also demonstrated promising maternal-fetal benefits of exercise during pregnancy such as improved physical fitness [12], more appropriate gestational weight gain [13], a decreased risk for preeclampsia and other pregnancy-specific diseases like gestational diabetes [14, 15], and decreased odds of macrosomia at birth without affecting the odds of growth-restricted, preterm, or low birth weight babies [12, 16, 17]. Studies have demonstrated that adherence to a Mediterranean diet, characterized by higher intake of unsaturated fats, lower intake of animal fats, and lower ratios of omega-6 to omega-3 fatty acids [18], is also associated with a reduced risk of many chronic diseases [19], improved fertility rates [odds ratio 1.4, 95% CI: 1.0–1.9] [20], as well as larger embryo yield in IVF [21], and better pregnancy outcomes [7, 20, 22, 23].

Despite the evidence of a healthier diet improving IVF procedure outcomes, there is little evidence on the molecular changes at the level of the oocyte or follicular fluid that occur due to alterations in diet, and virtually nothing is known about the impact of the combined effect of healthy diet and increased PA. Thus, we have designed a study with the primary objective of assessing the efficacy of a peri-conception nutrition and exercise intervention on mitigating obesity-associated changes in oocyte gene expression profiles and follicular fluid metabolites. Secondary objectives include determining the effect of the intervention on cumulus cells gene expression as well as the feasibility and acceptability of the intervention (using a standardized taxonomy [24]). To help address these objectives, overall metabolic health indices such as fitness, blood pressure, insulin sensitivity, triglycerides, C-reactive protein and interleukin-6 concentrations will be assessed.

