##### Biological samples

Blood samples, up to 35 ml, will be collected from the participants at visits 1 and 3 by a trained phlebotomist under overnight fasted conditions. During the entire study, we will collect up to 70 ml total. Blood samples will be centrifuged to separate plasma, serum, and red blood cells. Blood samples will be used to assess glucose, insulin, HOMA-insulin resistance score, interleukin-6, C-Reactive Protein, tumor necrosis factor, leptin, lipid profiles or any other biomarkers or analytes of interest using ELISA, electrochemiluminescence (ECL), colorimetric assays, metabolomics or any other appropriate methodology. Urine and stool collection will be obtained to evaluate metabolites, hormones or bacteria/microbes. Samples will be obtained using sterile collection cups. All biological samples will be aliquoted and stored at − 80 °C until further analyses.

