##### Oocyte, cumulus cell, and follicular fluid data collection

AF&GA will provide the research team with oocytes (eggs), cumulus cells (cells surrounding the egg), and follicular fluid (liquid surrounding the egg that also contains granulosa cells) that are not needed for the IVF procedures (e.g., too many eggs retrieved). These samples will be collected during the standard oocyte retrieval procedures performed as part of standard care for the participants undergoing fertility treatment. Participants will undergo standard procedures at AF&GA for ovarian stimulation, which include hormonal superovulation and oocyte retrieval 36 h after human gonadotropin injection. Any deviations from the standard clinic procedures will be documented and sensitivity analyses will be performed to determine whether deviations to stimulation protocol yielded in significant differences. It is possible that the research team will not obtain samples in the case that the retrieval yields only enough eggs for the IVF procedures. In this case, only follicular fluid will be obtained. The research team will not obtain samples that could have been fertilized or frozen as agreed with the participant prior to the retrieval procedure. The research team will obtain only samples that are unneeded by the clinic. Thus, no additional treatment or clinical procedures will be required for the participants. The embryologist at the clinic will collect the cumulus cells during the processing of the oocytes. Granulosa cells will be isolated from the follicular fluid by centrifugation at 4000 rpm for 10 min. Follicular fluid samples contaminated with blood will not be used for analysis. Samples will be placed on ice and transported by the research team to the ACNC where they will be stored in messenger RNA lysis buffer and frozen at − 70 °C until processing. Oocytes and cumulus cells will be used to study gene expression while follicular fluid will be used to measure metabolites and hormones that may be influenced by diet and exercise. Both mRNA and genomic DNA will be isolated from individual oocytes as previously described [9]. cDNA libraries will be prepared and fragmented cDNA will be evaluated to determine size distribution of the libraries. Samples will be sequenced using the NextSeq 500 System (Illumina). Individual libraries will be generated and RNA-Seq will be conducted. Sequencing reads from each sample will be trimmed and filtered before being aligned to the human genome (hg19). All data will be analyzed using SeqMonk and R software. Differentially expressed gene expression will be identified using the DESeq2 package which will include multiple testing corrections. Serum and follicular fluid glucose, total cholesterol, and triglyceride levels will be assessed using colorimetric or electrochemiluminescence assays. Serum and follicular fluid insulin, leptin, tumor necrosis factor (TNF)-α, C-reactive protein (CRP), and interleukin-6 will be measured using enzyme-linked immunosorbent or electrochemiluminescence assay kits. Serum lipid profiles—non-esterified fatty acids, high-density lipoprotein, and low-density lipoprotein— will be analyzed by enzymatic methods on a clinical analyzer. All assays will be performed in accordance with the manufacturers’ instructions.

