#### Sample size

Based upon existing data in the literature, a power of 0.8, and a *p*-value set at 0.05, with 20 women per group, we will be able to detect a mean difference of at least 0.37 standard deviation units in follicular levels of C-reactive protein and of insulin. In our previous study, we found follicular fluid CRP differences of 3.2 μg/ml (2.7 vs. 5.9 μg/ml, respectively) between normal weight and obese women [12]. Thus, we are confident that this sample size will be sufficient to detect clinically meaningful differences. Based on our experience, we expect that we will be unsuccessful in obtaining a good quality oocyte from approximately 33% of women enrolled. Therefore, we will enroll 30 women in each of the 4 groups (PCOS- standard of care, PCOS-intervention, no PCOS- standard of care, no PCOS-intervention) to assure that we will have at least 20 oocytes per group.

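### The primary follicular-fluid outcome is a class of eight listed analytes with none designated and no stated error control across them, and the one analyte with a predicted direction (IPA) has no named follicular-fluid assay

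*Protocol article*

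**What the plan says.** All references are to the protocol article.

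- **Outcome.** The Abstract (Methods) states: "Primary outcomes will include single oocyte gene expression profiles and follicular fluid metabolites". The primary objective in the Background has the same scope: "mitigating obesity-associated changes in oocyte gene expression profiles and follicular fluid metabolites". Neither names an analyte.
- **Assays.** The section on oocyte, cumulus cell and follicular fluid data collection names three analytes in one sentence ("Serum and follicular fluid glucose, total cholesterol, and triglyceride levels will be assessed using colorimetric or electrochemiluminescence assays") and five in the next ("Serum and follicular fluid insulin, leptin, tumor necrosis factor (TNF)-α, C-reactive protein (CRP), and interleukin-6 will be measured"). That makes eight in follicular fluid. The same section also says, in general terms, that the fluid serves to measure metabolites and hormones.
- **Sample size.** With 20 women per group, the trial is said to "detect a mean difference of at least 0.37 standard deviation units in follicular levels of C-reactive protein and of insulin".
- **Analysis.** Statistical analyses specifies a one-factor ANCOVA at four levels, Tukey-Kramer pairwise comparisons holding a 5% family-wise rate, and significance at p < 0.05. The other multiple-testing corrections mentioned in the article concern DESeq2 and the ontology, transcription-factor and pathway analyses.
- **Expectation.** For follicular fluid, the Discussion predicts one result: "lower Indole-3-Proprionic Acid (IPA) content in follicular fluid compared to women who received the standard of care". IPA appears elsewhere only in the abbreviation list.

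**The concern.** An outcome described as a class lets any member of the class carry the primary claim. Eight analytes qualify, and nothing in the text ranks them. A significant leptin or glucose result could be reported as the primary finding while CRP and insulin, the analytes that justify the number of women, show nothing. The stated family-wise rate does not prevent this, because it is held across the four groups for one analyte at a time.

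IPA raises a second issue. It is the only follicular-fluid analyte given an expected direction, and the Discussion pairs it with oocyte gene expression, much as the two primary outcomes are paired. A reader would expect to find its assay among the follicular-fluid measurements, and it is not named there.

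**Working it through.** **1. The plan's own figures.** The inflation for failed oocytes reproduces: 20 / (1 − 0.33) = 29.9, so 30 per group. The detectable difference of 0.37 SD does not. With n = 20 per group, two-sided 0.05 and power 0.80, it is √(2/20) × (1.960 + 0.842) = 0.89 SD (0.91 SD with the t distribution). Pooling the PCOS strata, 40 against 40, gives √(2/40) × 2.802 = 0.63 SD. This is a separate problem, and the steps below do not use 0.37.

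**2. Count of analytes.** Glucose, total cholesterol and triglycerides make 3. Insulin, leptin, TNF-α, CRP and IL-6 make 5. The total is 8. CRP and insulin are both in the list; IPA is not.

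**3. Scope of the stated error control.** Tukey-Kramer holds 5% over the pairwise comparisons of four groups for one analyte. Each analyte therefore carries its own 5%.

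**4. False positives across analytes.** Suppose there is no true effect, each analyte is judged once at two-sided 0.05, and any one significant analyte is read as a positive primary result.

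- Independent analytes: 1 − 0.95^8 = 1 − 0.663 = 0.337.
- Correlated analytes: the article gives no correlations, so a common value was assumed and the chance that any of eight |z| values exceeds 1.96 was simulated (400,000 runs).

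| Assumed correlation | Chance of at least one false positive |
|---|---|
| 0 | 34% |
| 0.3 | 30% |
| 0.5 | 25% |
| 0.8 | 16% |

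For CRP and insulin alone, without correction and independent: 1 − 0.95² = 9.75%.

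**5. Price of control.** Detectable differences by the normal approximation at power 0.80, using √(2/n) × (z for the stated alpha + 0.842):

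| Alpha per analyte | z | 20 per group | 40 per arm |
|---|---|---|---|
| 0.05 (no correction) | 1.960 | 0.89 SD | 0.63 SD |
| 0.025 (first Holm step, two analytes) | 2.241 | 0.316 × 3.083 = 0.97 SD | 0.224 × 3.083 = 0.69 SD |
| 0.00625 (Bonferroni, eight analytes) | 2.734 | 1.13 SD | 0.80 SD |

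Designating two analytes costs far less than correcting over all eight.

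**6. IPA.** Metabolomics is named once, in Biological samples ("colorimetric assays, metabolomics or any other appropriate methodology"), where the sentence concerns blood. The follicular-fluid sentences name colorimetric, electrochemiluminescence and enzyme-linked immunosorbent methods for the eight analytes above.

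**The case against.** Several stronger readings are tempting, and the article does not support them.

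- **That the endpoint is three contradictory things.** CRP and insulin are in the assay list and fall under the planned analysis. Sizing a trial on two of the measured analytes is not a contradiction. Calling them metabolites is loose wording at most.
- **That IPA is the trial's hypothesis and cannot be tested.** IPA is an expectation in the Discussion. The objectives, outcomes, analysis and sample size do not mention it. The general wording on metabolites and hormones is open, and a journal article may leave the full assay panel to the complete protocol. What can be said is that the article names no follicular-fluid assay for it.
- **That 34% refutes a stated 5%.** The stated 5% belongs to group comparisons within an analyte, and the article promises no rate across analytes. It also states no rule that one significant analyte makes the primary outcome positive. The 34% is conditional on that reading and is the independence value; strong correlation brings it down to about 16%.

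It can also be said that a statistical analysis plan may add correction across analytes. That is fair for the method of correction. Which analyte is primary, however, is a protocol-level choice, and here it is fixed only as a class. That part of the concern stands, as does the missing IPA assay.

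**Conclusion.** The concern holds in a limited form. The primary follicular-fluid outcome does not single out an analyte, eight are listed, two carry the sample size, and the stated error control stops at the boundary of one analyte. Read in the way this wording permits, the chance of at least one false-positive primary analyte lies between about 16% and 34%. That range rests on four assumptions: no true effects, one two-sided 0.05 judgement per analyte, an any-analyte success rule that the article does not itself state, and assumed correlations from 0.8 down to 0.

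Separately, the prediction for IPA and the named assays need to be reconciled. This is a mismatch within the article, not proof that IPA will go unmeasured.

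**What to change.** 1. Reword the primary follicular-fluid outcome to follicular-fluid CRP and insulin, the analytes already used for the sample size. Test them with Holm at 5% overall: the smaller p-value against 0.025, then the other against 0.05. Holm needs one p-value per analyte, so state which test supplies it.
2. Make glucose, total cholesterol, triglycerides, leptin, TNF-α and IL-6 secondary, with false discovery rate control.
3. For IPA, either name a follicular-fluid assay and list it as a secondary endpoint with a two-sided test, or remove the prediction from the Discussion. The first option depends on whether the stored fluid allows it: the article gives no fluid volume, discards blood-contaminated fluid, and describes storage in an RNA lysis buffer. Because Data management rules out future research on the samples, the assay would have to be specified within this study.
4. Correct the 0.37 SD figure before using it to support CRP and insulin as primary endpoints.

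The cost is protocol and registry wording, plus one assay if IPA is kept. The downsides are that a significant result on another analyte can no longer be called a primary finding, and that the first Holm step raises the detectable difference from 0.89 to 0.97 SD at 20 per group. Choosing CRP and insulin together, and not CRP alone, is a judgement; it follows the sample-size section as written.

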### Strengths

This is a robustly designed RCT that uses valid and reliable measures with standardized procedures and quality control measures. Strengths of this study lie with ease of compliance during the 8–12 week exercise and nutrition intervention, with the majority of food shipped directly to the participant, and all exercises being self-directed and accessed through an application on the participant’s phone or computer. In addition, the participant’s engagement with health coaches will increase adherence and compliance.

### Contingencies

Recruitment may be challenging because we will be enrolling women who want to conceive as soon as possible and who may choose to immediately attempt in vitro fertilization rather than wait. However, these women will have a high motivation to achieve the best outcomes for their treatments, which are known to be improved by increasing physical activity and adhering to a healthy diet.

Sedentary women with obesity may also be reluctant to participate in PA or implement dietary changes. To counter compliance issues, participants will have twice-weekly phone contact with the trained professionals at ACNC. We believe participants randomized to the intervention group will have a higher rate of participation due to their urgency to conceive and lack of pregnancy symptoms that can make it more difficult to engage in exercise routines. While we will track diet compliance through daily food diaries, this approach cannot fully capture non-compliance with the dietary intervention. For this reason, we will collect red blood cells for analysis of enrichment in PUFAs in the intervention groups. Stool will also be collected to enable a secondary measure of microbiome differences across groups. We anticipate that intervention participants, whose diet will contain significantly more fiber, fruits, and vegetables compared to the typical American diet, should be readily distinguishable from the control group.

The research team at the ACNC has experience in all aspects of the proposed study. Therefore, minimal problems are expected regarding the techniques proposed. One potential concern is participant non-compliance or drop out. Accordingly, we anticipated this issue in our sample size calculation. Absence of an effect of the intervention is also a concern; in this case, a study with a longer intervention or an additional exercise intervention would be explored for future studies.

